### Transit beliefs and perceptions

We developed and evaluated a survey based on theory-driven behavior change determinants, adapted to relate specifically to LRT use, to understand how attitudes and perceptions shift over time after campus reopened from COVID-19 closures. Using the Social Cognitive Theory [102] and Transtheoretical Model [103], survey measures assess the following constructs: intentions to use LRT, benefits (e.g. health, cost, climate) and barriers to use (e.g. access, schedules, safety), social support (e.g. family/coworkers use or encourage LRT use), satisfaction with transit service (e.g. hours, frequency, access, stops) and COVID-19 safety measures (e.g. ventilation systems, touchless pay stations, sanitization procedures), self-efficacy (e.g. confidence in ability to use transit safely), outcome expectancy (e.g. effectiveness of COVID-19 mitigation measures), and COVID-19 infection and vaccination status.

### Covariates and effect modifiers

Sociodemographics include age, sex, race/ethnicity, education, marital status, annual household income, number of adults and children in the household, vehicle access, driving status, caretaking/childcare responsibilities, and years living at address. Health Status will be measured with a subset of the NHANES ‘medical conditions’ survey [104]. An 18-item questionnaire that measures reasons for moving to your neighborhood will be used to adjust for residential self-selection, which is a potential bias in environmental studies [105].

### Environmental effect modifiers

We will use the US Environmental Protection Agency’s Smart Location Database (SLD) of key built and social environment variables for all census block groups and the areas around LRT stations [106, 107]. These GIS data include variables for: Density (population, employment, housing, etc.); Diversity (mixture of uses, incomes, etc.); Design (walkability/intersection density), and Destination Accessibility (number of jobs accessible by transit and auto). Proximity to the trolley line of residential and occupational addresses will be calculated using GIS from geocoded locations. Neighborhood perceptions around home locations will be measured by self-report using the validated and widely used Neighborhood Environment Walkability Scale (NEWS)—Abbreviated survey [108–110] which has been associated with AT in adults [111].

### Statistical approach

Summary statistics of individual-level demographics, census block attributes, and baseline values of all outcomes will be calculated for the full sample and compared between the LRT exposure groups. Variables that are not balanced across groups will be adjusted for in subsequent analyses. Daily minutes of MVPA are typically positively skewed and will be transformed as needed to better approximate normality. Longitudinal changes in outcomes across the 3 measurement time points will be assessed using multilevel mixed effects linear (for continuous outcomes) or multinomial or ordinal logistic (for categorical outcomes) regression models, with the measurement time point included as an independent variable and adjustment for individual or block group level covariates (i.e., demographic characteristics, walkability, etc.). Covariates will be selected using a priori-knowledge and Directed Acyclic Graphs. Each outcome will be modeled separately. As we will have multiple measurement days nested within participants, a random participant-level intercept will be included in all models (alternative approaches that consider such clustering based on generalized estimation equations (GEE) will be also tested as a sensitivity analysis). We will also test the extent of block group clustering for each outcome (without covariates) by including a random effect for the intercept at the block group level and estimating the intra-class correlation (ICC). A likelihood-ratio test will assess fit between the models with and without clustering and, if significant, a random effect for block group will be included. We will assess effect modification by LRT exposure and other variables on both additive and multiplicative scales (when focusing on binary, categorical or count outcomes) using traditional approaches (stratified analyses coupled with heterogeneity tests or by including an interaction term in our models) [112, 113].

We will perform additional sensitivity analyses to maximize covariate balance between LRT groups, considering techniques like inverse probability of treatment weighting (IPTW). IPTW removes confounding by creating a pseudo population in which every participant has an equal probability of being in the LRT- exposed group (i.e., home < 1 mile from LRT stop), assuming no unmeasured confounding. We will first model participants’ probability (i.e. the propensity score (PS) of being in the LRT-exposed group) [114] using imbalanced baseline demographic and environmental characteristics [115–117]. We will then calculate a weight using the PS values that will be included in regression models. Estimates from weighted and unweighted models will be compared and will also implement stabilized and truncated weights. We will examine the extent of missing data and conduct sensitivity analyses to compare characteristics of participants with complete versus incomplete data. Multiple imputation methods will be applied, assuming missing-at-random patterns and using default multiple imputation models (“mice” in R), with *N* imputed data sets generated (*N* corresponding the average % of missingness).

Test–retest reliability of the transit and COVID-19 survey measures, with two weeks in between assessments, will be assessed using intraclass correlation coefficients (ICC) [118, 119]*.* Values above 0.75 will be considered good to excellent reliability.

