## Methods/Design

### TROLLEY Study Design and Setting

TROLLEY is a prospective cohort study of 465 adults working at UC San Diego (UCSD) at 3 time points over 2 years of follow up. The new 11-mile UC San Diego Blue Line light rail extension opened in November 2021. This new line connected transit-served low-income and diverse communities in south and east San Diego County, where a large proportion of UCSD’s roughly 18,000 staff reside, to the major employment, education, and healthcare center of UCSD. The trolley line was completed prior to participant enrollment. However, data on travel, health and spending behaviors before COVID-19 and the LRT line opening will be collected retrospectively to allow for a pre-post comparison. UCSD is San Diego County’s second largest employer with a majority of staff from racial or ethnic minority groups and 90% filling non-managerial roles [58]. The new LRT line has three stops accessing the UCSD La Jolla campus and the VA and UCSD medical centers, providing a functional transportation option for university and healthcare workers. Unlike previous LRT intervention studies that recruited people around new stations that may or may not connect them with employment destinations [59–66], we will recruit staff who work near LRT and live either within 1 mile, 1–2 miles, or  > 2 miles from any San Diego LRT station. Previous research has long shown that environmental features at both home and work locations are significantly related with travel mode choice [67]. Therefore, the sampling design we proposed has greater potential to capture the impact on commute travel patterns.

The TROLLEY study framework, summarized in Fig. 1, is based on multilevel ecological models that highlight the many levels of influence on active living behaviors [68].

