### Data collection

Participants will complete a measurement visit after consenting to participation. Participants will be assessed 3 times during the 2 years they are enrolled in the study; once when first enrolled (2022), 1 year after enrollment (2023), and 2 years after enrollment (2024). All data collection will occur after the opening of the UCSD Blue Line Trolley. However, time 1 survey measures ask participants about commute, PA, and spending behaviors both at the time of assessment and, retrospectively, prior to the pandemic and the new LRT. The campus closure in March of 2020 due to COVID-19 provides a noteworthy reference point to aid recall. The UCSD Exercise and Physical Activity Resource Center (EPARC) distributes accelerometer and GPS devices and instructs participants how to wear the monitors. TROLLEY staff call participants during the wear week to ensure compliance. Links to the online surveys are emailed to participants, and participants receive a $50 gift card after completion of all assessments at each time point.

Study data are collected and managed using REDCap electronic data capture tools hosted at UC San Diego [79]. REDCap (Research Electronic Data Capture) is a secure, web-based application designed to support data capture for research studies, providing: 1) an intuitive interface for validated data entry; 2) audit trails for tracking data manipulation and export procedures; 3) automated export procedures for seamless data downloads to common statistical packages; and 4) procedures for importing data from external sources. Participants are assigned a study ID and all records are coded with the study ID rather than personal identifiers. All device data files will be kept on secure servers at the Social Sciences Computing Facility and data will only be accessible to investigators and project staff.

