## Discussion

The TROLLEY study has a unique opportunity to quantify change in key travel, health, and equity-related outcomes associated with the introduction of new LRT infrastructure and in the context of the COVID-19 pandemic. Research is needed to explore variables that may prevent increased vehicle dependence as a long-term consequence of the pandemic [53], and inform interventions to improve individual and climate health indicators. Despite promising cross-sectional evidence of associations between LRT and health, including MVPA, longitudinal evidence is less consistent [31, 36, 38, 120–122]. The TROLLEY study has the potential to document a more powerful effect than previous LRT evaluation studies based on the unique sampling of employees whose work location is newly accessed by LRT and who live near an LRT station. Low-income communities bear a greater burden from transportation costs and reliance on vehicles that negatively impacts health. Improving transit access may provide a cost-effective and long lasting approach to improve PA and health, with broad reach to lower income employees [123]. The TROLLEY study will improve our understanding of the mobility needs of vulnerable groups and transit as a workplace health and equity strategy.

The 2-year length of the study presents a challenge to participant retention. While we have planned for 20% attrition, the university sample allows more opportunity to maintain contact with participants and mitigate loss to follow up. The lack of accelerometer and GPS device data prior to the opening of the new LRT line limits our ability to detect true prospective associations between LRT and the outcomes under study. However, self-reported measures are likely to capture commute mode and frequency with sufficient accuracy to provide insight into change over time and the stratified sampling strategy and large sample size allow us to determine whether LRT, sociodemographic, and environmental factors modify change in outcomes. The state-of-the-science objective measures of PA, travel behavior, and built environments, in conjunction with 2-years of follow, strengthen our ability to capture a gradual uptake of LRT use and change in behaviors as the pandemic evolves.

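### The plan gives two covariate rules without precedence; one admits post-opening Time 1 outcomes as covariates, and the sensitivity propensity score draws only on imbalanced variables

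*Protocol article*

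**What the plan says.** All of the selection rules stand in the Protocol article under *Statistical approach*.

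- **What is screened.** Demographics and census-block attributes are summarised, and "baseline values of all outcomes will be calculated for the full sample and compared between the LRT exposure groups".
- **Imbalance rule.** The next sentence reads "Variables that are not balanced across groups will be adjusted for in subsequent analyses". It gives no criterion for imbalance and exempts no class of variable.
- **DAG rule.** A few sentences later: "Covariates will be selected using a priori-knowledge and Directed Acyclic Graphs". Neither rule is given precedence.
- **Propensity score.** A sensitivity analysis with inverse probability weighting models the chance of living within 1 mile of a stop, "using imbalanced baseline demographic and environmental characteristics". The same paragraph says the method assumes that no confounder is unmeasured.

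Three other sections bear on the point.

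- **Timing.** *Data collection* says "All data collection will occur after the opening of the UCSD Blue Line Trolley", and *TROLLEY Study Design and Setting* says "The trolley line was completed prior to participant enrollment". The *Discussion* concedes the consequence: "The lack of accelerometer and GPS device data prior to the opening of the new LRT line limits our ability".
- **Recalled data.** Under *Data collection*, the T1 survey also asks about commuting, physical activity and spending before the pandemic and the new line.
- **Self-selection.** Under *Covariates and effect modifiers*, an 18-item questionnaire on reasons for choosing the neighbourhood "will be used to adjust for residential self-selection, which is a potential bias in environmental studies".

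**The concern.** Home distance to LRT is not randomised, so the choice of covariates matters to any comparison between distance groups. Two features of the stated rules are unsound.

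First, read literally, the imbalance rule reaches T1 outcomes. If the line has already changed activity, travel mode or VMT by T1, the groups differ at T1 because of the exposure. The rule would then treat part of the effect as an imbalance to be removed. A DAG for the effect of LRT access would not admit a consequence of exposure as a confounder, so for these variables the two rules conflict. The T1 value is also one of the three responses in the same model.

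Second, the propensity score filters its inputs by observed imbalance and limits them to two classes of variable. Its weights can therefore leave out confounders that the study measures, although the method rests on confounding being fully captured.

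With both rules in force and no order between them, an analyst could defend either covariate set after seeing the data.

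**Working it through.** The plan states no figure on this point, so there is none to reproduce. The check compares the passages and then sizes the consequence under assumed values.

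**1. Is T1 post-exposure?** Yes. The line opened in November 2021, recruitment began in January 2022, and all three waves follow. Only self-reported commuting, activity and spending have a recalled pre-opening value. The device outcomes have none.

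**2. Do the rules conflict?** For pre-exposure variables they can be read together, as a DAG set plus whatever else is imbalanced. For T1 outcomes they cannot: one admits an imbalanced T1 outcome and the other would exclude it.

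**3. Effect of using the T1 outcome as a covariate.**

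From the document: 465 participants, equally split over three distance groups, so 465/3 = 155 per group. Assumed: between-person SD 1 and residual SD 1, giving wave-to-wave reliability r = 1/(1 + 1) = 0.5. Group effects t1, t2, t3 at the three waves are in units of the between-person SD.

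- T3 difference adjusted for T1 = t3 − r × t1
- Average difference over three waves with T1 as covariate = mean(t) − [r + (1 − r)/3] × t1, where the bracket is 0.5 + 0.5/3 = 0.667

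| Scenario | Quantity | Without T1 | With T1, formula | With T1, simulated (2,000 runs) |
|---|---|---|---|---|
| Effect 0.5 at every wave | T3 difference | 0.50 | 0.50 − 0.5 × 0.50 = 0.25 | 0.24 |
| | Average over waves | 0.50 | 0.50 − 0.667 × 0.50 = 0.17 | 0.16 |
| | Time-by-LRT interaction (T3 vs T1) | 0 (simulated −0.01) | unchanged | −0.01 |
| Gradual: 0.25, 0.375, 0.5 | T3 difference | 0.50 | 0.50 − 0.5 × 0.25 = 0.375 | 0.37 |
| | Average over waves | 0.375 | 0.375 − 0.667 × 0.25 = 0.21 | 0.21 |
| | Time-by-LRT interaction (T3 vs T1) | 0.25 | unchanged | 0.25 |

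The loss grows with reliability. For a constant group difference, the share of the average removed is r + (1 − r)/3: 0.73 at r = 0.6 and 0.87 at r = 0.8.

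The interaction does not move because the T1 value is constant across a person's three records. Entered as a main effect, it is unrelated to within-person change, and with complete data the interaction is estimated from that change alone.

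**4. Effect of the imbalance filter.**

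The document gives no criterion for imbalance; p < 0.05 is assumed here. For a confounder with a true standardised difference of 0.2:

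- 155 against 155: SE = √(2/155) = 0.114, z = 0.2/0.114 = 1.76, so it is missed with probability about Φ(1.96 − 1.76) = 0.58 (simulated about 0.57, 4,000 runs).
- 155 against 310 (the under-1-mile group against the other two): SE = √(1/155 + 1/310) = 0.098, z = 2.03, missed with probability about Φ(1.96 − 2.03) = 0.47.

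With 155 against 155, the simulation adjusted for the confounder by regression only when it was flagged. A one-SD rise in the confounder was assumed to shift the outcome by 0.5 or 1.0 residual SD. The mean bias was 0.04 and 0.07 residual SD respectively, and type I error was 0.053 and 0.060. With the confounder always adjusted for, type I error was 0.044 and 0.054. At a 0.1 SD difference the confounder was missed in about 86% of runs, with bias 0.04 to 0.06.

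**The case against.** The strongest reply is that the plan targets change over time and its modification by LRT exposure, with T1 as one of three responses. A T1 covariate leaves that contrast alone in the linear model. This stands, and it limits the harm to group level differences, averages over waves and any T1-adjusted comparison. The check covers complete data and linear models; it says nothing about the logistic models planned for categorical outcomes.

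It can also be said that the authors do not mean to enter outcomes as covariates. The model covariates they give as examples are demographics and walkability, and the propensity score names no outcomes. That is a fair reading of intent, but the sentence follows directly on the comparison of outcome values and exempts nothing.

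Third, a reader might infer that the main models will omit real confounders. The text does not support this. It says imbalanced variables are adjusted for, not that balanced ones are dropped. The DAG set remains, and adjustment for self-selection is promised without any balance condition. The omission applies to the propensity score, which is a sensitivity analysis, and the weighted regressions may still carry the other covariates. One could also stretch the word environmental to cover the self-selection scale, but the text does not say so.

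Fourth, a reader might take conditioning on T1 to manufacture a difference in change of 1 − r, or 20 to 40% of the T1 gap at reliability 0.6 to 0.8. That needs a follow-up model with T1 as covariate, which is not planned. The document also gives no T1 gap to apply it to: its 3.46 min/day is an expected change in transit-related activity.

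**Conclusion.** The concern holds in limited form. The section states two selection rules without precedence, and one of them, taken literally, admits a post-exposure response as a covariate. If followed, it would shrink level or T1-adjusted contrasts; the fall from 0.50 to 0.24 rests on assumed equal between-person and residual variances and an effect fully present by T1. The stronger conclusion, that the plan would adjust away its LRT effect, is not supported: the planned time-by-LRT interaction is unchanged in a balanced linear mixed model. The loss of 73 to 87% at reliability 0.6 to 0.8 likewise belongs to an average level difference, not to that interaction.

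The propensity score, as worded, leaves out measured candidate confounders and any variable that does not look imbalanced. The miss rate of about 58% depends on a p < 0.05 screen that the plan does not state, and the illustrated bias from one missed confounder is small. The point should be corrected because a data-driven rule remains where a pre-specified one is already promised; it does not invalidate the main analysis.

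**What to change.** - Delete the imbalance rule, or limit it to pre-exposure variables that the DAG admits, and state that the DAG governs.
- State that T1 outcomes enter the models as responses only and never as covariates.
- Build the propensity score from the same DAG-based confounder set whatever the observed balance, including the residential self-selection scale and recalled pre-LRT commuting and physical activity.
- Keep the balance tables for description only.

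The cost is protocol or SAP wording and slightly more covariates in the models. No new data are needed, since the self-selection scale and the recalled items are already collected.

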**Fig. 2 Fig2:**
[figure not shown]
LRT stations with recruitment catchment areas MTS LRT stations (red), census block groups within one mile with at least 25% area overlap with station areas (green), block groups between one and two miles (white), block groups greater than 2 miles (no-LRT-group) with at least 25% area overlap with two-mile catchment areas (beige). Figure created by authors

The primary recruitment strategy is to identify interested and eligible staff through a pre-screening survey invitation sent by UCSD’s Department of Resource, Management and Planning, in both English and Spanish. The email was sent to > 17,000 active UCSD career staff, identified by their job title code. This method allows us to target staff specifically, exclusive of students and faculty. The email contains an embedded link to the study screener from our secure study database. Those who choose to complete the pre-screening survey provide their contact information, home address or nearest intersection, and answer the eligibility screening questions. The home addresses of staff who meet the initial screening criteria are then geocoded and spatially joined to the recruitment catchment buffers to determine which catchment area they live in. Those who are not eligible receive an email and a phone call explaining the reasons for ineligibility. Those who meet eligibility criteria are contacted by research staff who confirm interest and eligibility, answer questions, and obtain written informed consent.

In addition to university email, we are recruiting through UCSD staff distribution listservs and flyers, staff associations and unions, and on-campus advertising. These recruitment efforts target key UCSD units like Housing, Dining and Hospitality services, the Black, Chicanx/Latinx, and Pan-Asian Staff Associations, and hospital nursing and support staff groups to reach the intended population. Recruitment began in January 2022 and is ongoing, with 230 participants currently enrolled.

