### Sample size

The TROLLEY study will enroll 465 English or Spanish speaking staff from UCSD’s La Jolla campus. We estimated a sample size of 340 was needed, considering a baseline of 45.1 (SD: 4.6) minutes/week of moderate PA using NHANES (2005–06) adult accelerometer data. We used a meta-analysis by Hirsh et al. and a conservative expected change of 3.46 min/day (95%CI: 2.20, 4.72) in transit-related PA from Miller et al. that evaluated a similar intervention in Utah [62, 78]. We set a significance level of 0.05 and power levels of 95% and assumed a 20% attrition rate. However, to ensure sufficient power for planned moderator analyses and in case of higher attrition rates than planned, we will recruit a total sample of 465 participants, stratified by LRT exposure, income, and race/ethnicity.

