### Self-report measures and covariates

#### Equity Outcomes

Household expenditures and transportation costs will be assessed by self-report using survey measures from the Health and Retirement Study [87]. The Consumption and Activities Mail Survey captures information about healthcare, food, and transportation expenditures. The Health Care and Nutrition Survey considers whether health care access and nutrition spending were impacted by income (e.g., “In the last 12 months, did you ever eat less that you felt you should because there wasn’t enough money for food?”). All participants will be employed at baseline, but we will ask about changes in employment at all future assessments. Secondary human resource data will capture summary measures of new employees during the project period to determine the impact of the LRT line on employment opportunities (for example, a summary measure of the percentage of new employees using LRT as their primary commute method). Health care access and utilization will be assessed using questions from the Behavioral Risk Factor Surveillance System (BRFSS) survey.

Secondary health outcomes will be evaluated using validated self-report measures. We will use the 10-item Center for Epidemiological Studies-Depression Scale (CES-D Short-form), which is a commonly used population-based scale for measuring depressive symptoms in adults [88–90]. The 20-item Perceived Quality of Life scale (PQoL-20) asks participants to rate their satisfaction with various aspects of life [91], and the SF-12 Health Survey will measure health-related QoL [92, 93]. The Cohen Perceived Stress Scale measures the degree to which situations in one’s life are perceived as stressful [94]. To better understand sources of stress from discrimination and racism in our cohort, we included an additional measure of stress. The validated Everyday Discrimination Scale asks how often participants experience discrimination in their daily life based on their race, ethnicity or skin color [95–97]. The NIH PROMIS Sleep Disturbance 6a Short Form will assess perceptions of sleep quality, sleep depth, and restoration [98]. The Global Physical Activity Questionnaire allows us to capture self-reported PA in the occupational, transportation, and leisure domains [99, 100]. Participants will self-report height and weight, and BMI will be calculated (kg/m^2^) [101].

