Due to continued COVID-19 surges, the return to on-campus work has been slower than anticipated. As of summer 2022, student instruction and working arrangements remain an in-person and remote hybrid, making the distribution of devices more challenging. Given COVID-19 safety protocols, limited research staff have been working in-office to answer the recruitment phone line, and many measurement appointments have been rescheduled due to participant illness, childcare duties, or changes in staff scheduling. In response, we’ve expanded our device distribution locations so we can meet participants at more convenient campus locations.

Trolley ridership within the San Diego Region is reported at approximately 80% compared to pre-pandemic periods [124]. Multiple factors beyond the introduction of a new LRT line have likely impacted transit usage during the study period, including increased gas prices and changes in transit pass costs. Our surveys and analyses will attempt to capture and explore these factors.

We anticipate difficulty in achieving recruitment goals across income and racial strata as essential workers and people of color have experienced greater stress and negative health impacts due to the pandemic [125] and may have less capacity to participate. We have identified block groups with high concentrations of poverty and people of color to aid recruitment from these areas during the eligibility screening process. We will additionally employ outreach strategies to staff associations and unions representing diverse campus employees. We’ve met with leaders of these organizations to understand members’ concerns (e.g.., parking costs and availability, work schedules) so we can communicate how the study goals align with their interests. We have also formed an Advisory Board of stakeholders, including UCSD administration and staff/student representatives, staff from the City of San Diego, San Diego Association of Governments (SANDAG), and MTS, and representatives from local climate, mobility, and environmental justice advocacy organizations. We will partner with our extensive, interdisciplinary network of stakeholders to ensure the environmental justice and equity goals of the study are achieved, the research is relevant across sectors, and to share data and findings to help inform future investments in San Diego, California, and nationally.

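### Time is modelled by visit counted from each person's enrolment, while light rail uptake runs on calendar time from the November 2021 opening

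*Protocol article*

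**What the plan says.** **Opening and enrolment.** The study design section states: "The new 11-mile UC San Diego Blue Line light rail extension opened in November 2021". The recruitment section adds: "Recruitment began in January 2022 and is ongoing, with 230 participants currently enrolled". The target is given under Sample size: "we will recruit a total sample of 465 participants". The Discussion places the time of writing: "As of summer 2022, student instruction and working arrangements remain an in-person and remote hybrid".

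**Visits.** Under Data collection, participants are assessed "once when first enrolled (2022), 1 year after enrollment (2023), and 2 years after enrollment (2024". All three visits come after the opening.

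**Model.** Under Statistical approach, change over the three visits is estimated in mixed models "with the measurement time point included as an independent variable", with a random participant intercept. Effect modification by light rail exposure is tested by stratification or an interaction term.

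**Expectation.** The Discussion says that the measures and two years of follow-up "strengthen our ability to capture a gradual uptake of LRT use and change in behaviors as the pandemic evolves".

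**Look-back items.** Under Equity Outcomes, the article quotes one item with a 12-month window: "In the last 12 months, did you ever eat less that you felt you should because there wasn’t enough money for food".

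**The concern.** Uptake of a new line starts on one date for everyone, and so do the stages of pandemic recovery. Enrolment does not: at T1 one person may be in the first weeks of service and another more than a year into it. A visit term treats both as the same point in time.

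Two things are at stake. First, the visit coefficient becomes an average over different parts of the uptake curve, and the spread in T1 dates, which carries information on early uptake, goes unused. Second, the hypothesis under Study Aims compares change between people living closer to and farther from stations. If those groups enrolled at different times, part of their difference in change would come from enrolment timing.

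No stated safeguard covers this. The covariate list names neither enrolment date nor calendar date. The balance check concerns demographics, block attributes and baseline outcomes, and the propensity weights use demographic and environmental characteristics. The random intercept absorbs constant differences in level between people, but not differences in change over time.

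**Working it through.** The article gives no figure of its own on this point, so the check is date arithmetic followed by an illustration.

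**1. Months from opening to T1.** Inputs: opening in November 2021 (day not given, so 1 to 30 November is used), enrolment from January 2022, T1 in 2022. Months m = days from opening to T1 / 30.44. The share of a 12-month look-back lying before opening is max(0, 1 − m/12).

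| T1 date | Months after opening | Pre-opening share of a 12-month window |
|---|---|---|
| 1 January 2022 | 1.1 to 2.0 | 91% to 83% |
| 31 January 2022 | 2.0 to 3.0 | 83% to 75% |
| 21 June 2022 | 6.7 to 7.6 | 44% to 36% |
| 30 November 2022 | 12.0 to 12.9 | 0% |
| 31 December 2022 | 13.0 to 14.0 | 0% |

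T1 thus spans about 12 months of the uptake period, even when held strictly to 2022.

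**2. Is a spread over most of 2022 realistic?** Assume that the 230 were reached between 21 June and 22 September 2022, that is 5.6 to 8.7 months after 1 January. The pace is then 230/5.6 ≈ 41 to 230/8.7 ≈ 27 per month (rounded), and 465 is reached after about 11.4 to 17.5 months. Enrolment through most of 2022 is therefore to be expected. The upper end is extrapolation and is not used below.

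**3. What the visit contrast measures (illustration; the curve is assumed).** Let uptake be U(t) = 1 − 2^(−t/h), with t in months since opening and half-time h. The change from T1 to T3, 24 months later, is 2^(−m/h) × (1 − 2^(−24/h)), as a share of the full effect.

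- h = 6: the second factor is 1 − 2^(−4) = 0.9375. At m = 2: 0.794 × 0.9375 = 0.74. At m = 13: 0.223 × 0.9375 = 0.21.
- h = 12: the second factor is 1 − 2^(−2) = 0.75. At m = 2: 0.891 × 0.75 = 0.67. At m = 13: 0.472 × 0.75 = 0.35.

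These are individual extremes. They show how much the visit contrast mixes; they are not a bias between groups.

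**4. Difference between groups.** If one group's enrolment dates are shifted later by d months, its mean T1-to-T3 change is multiplied by 2^(−d/h). For an assumed d = 2:

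- h = 6: 2^(−2/6) = 0.79
- h = 12: 2^(−2/12) = 0.89

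So a 2-month shift would make that group's change look 21% or 11% smaller with no true difference in uptake.

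**The case against.** The strongest reply is that a condensed article need not settle how time is coded. Covariates are to be chosen from prior knowledge and causal diagrams, variables unbalanced between exposure groups are to be adjusted for, and the Discussion promises to explore outside influences such as fuel prices and pass costs. A fuller plan could add calendar terms. This stands in part. But the article does name the time variable, and the visit schedule ties it to personal enrolment however it is coded. Adjusting for enrolment date as a main effect would not help either, because the problem lies in change over time.

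Visits are 12 months apart within each person, so season is matched and the visit coefficient is a legitimate cohort-average change over the observed window. That stands, and it is why the visit term should be kept. The part of uptake lost before any T1 is a separate limitation, related to the absence of pre-opening device data that the authors concede.

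A reader might infer more than the documents support:

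- **That the distance contrast is biased.** The main recruitment route was one email to more than 17,000 staff regardless of distance. Targeted outreach concerned work units, staff associations, unions and block groups with high poverty or many people of color. Different enrolment dates by group are possible, but nothing shows them.
- **That enrolment ran past 2022.** The schedule puts T1 in 2022; anything later is extrapolation from an undated count.
- **That some T1 look-back windows lie wholly before opening.** None does; the earliest are 83% to 91% pre-opening. Only one such item is quoted. The primary outcomes come mainly from 7-day device wear, and commute, activity and spending also have a pre-pandemic recall that does not move with enrolment date.

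**Conclusion.** The point holds as a mismatch between the stated time variable and the process under study. That T1 runs from about 1 to 3 months up to 13 to 14 months after opening follows from the documents' own dates. The visit contrast therefore averages unlike stretches of an uptake that the authors call gradual.

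The harm to group comparisons is conditional on enrolment dates differing by group. Its illustrated size, a factor of 0.79 or 0.89 for a 2-month difference, rests on the assumed uptake curve, its half-time and the assumed shift. The matter is worth correcting before analysis, and it does not invalidate the design.

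**What to change.** - Keep the visit term for within-person change. Add months from opening to each participant's T1 and its interaction with visit. Alternatively, model months since opening with within-person and between-person components separated, plus month-of-year terms. A single months-since-opening term is not enough, because it pools differences between early and late enrolees with change within a person.
- Test distance group by time with these terms in the model.
- Report enrolment date by distance and income group.
- For 12-month look-back items, include the share of the window falling after opening. At T2 and T3 that share is 1 for everyone, and at T1 it equals m/12 up to 12 months. It is therefore almost a linear function of the months-to-T1 and visit terms, and in these models it should replace the months-to-T1 terms rather than sit beside them. Leave the item's reference period unchanged: with 230 already enrolled, altering it would mix windows across people and visits.

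The cost is a few extra model terms and slightly wider intervals. The visits are scheduled from enrolment, so the dates should already be on file. One limit remains: with a single opening date, months since opening is calendar time shifted by a constant. It cannot by itself separate rail uptake from pandemic recovery, and that attribution still rests on the distance-group contrast.
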